### **Pregnancy and Intrauterine Exposure**

To ensure the safety of the subject, pregnancy events occurring in the subject or the subjects' partner during treatment with the study drug or within 6 months after discontinuation of the study drug should be reported to the sponsor within 24 hours of awareness. Pregnant patients should be followed up to determine the pregnancy outcomes, including spontaneous abortion or voluntary termination of the pregnancy, details related to the birth of the infant, and the presence of birth defects, congenital abnormalities, or maternal genetic and/or neonatal complications.

Pregnancy events should be recorded on the clinical study pregnancy form, and reported by the investigator to the sponsor or its designee. Follow-up information of the pregnancy should be recorded on the same form, which should include an evaluation on the relationship between the study drug and the pregnancy outcome. All SAEs occurring during pregnancy must be recorded and reported on the Serious Adverse Events Report Form. Pregnancy outcomes of the female partners of the male subjects receiving study drug in this study must be collected. Informed consent regarding these pregnancy outcomes should be obtained from the mother when reporting.

Adverse pregnancy outcomes such as spontaneous abortion, fetal death, fetal malformation, stillbirth, birth defect, or congenital anomaly should be reported as SAEs.

**Overdose, Medication Error and Abuse**

An overdose is defined as more than 20% of the dose administered as specified in the protocol.

If a subject experiences an overdose, medication error, abuse, or misuse in the study, regardless of whether there is a relevant AE, the investigator should report it to the sponsor within 24 hours of awareness. If the above situations lead to SAEs, the investigator should report the SAEs.

## 9 DATA ANALYSIS AND STATISTICS

### STATISTICAL METHODS

Study results will be summarized using descriptive statistics, i.e., statistics for continuous variables may include mean, median, range, and standard deviation/variability. Qualitative variables will be summarized by counts and percentages. The uncertainty of estimates will be assessed by confidence intervals (CIs). The specific analytical methods will be described in the SAP.

### SAMPLE SIZE CALCULATION

In this study, 80-122 subjects are planned to be enrolled in the cohort treated with KN026 + KN046, including 30-36 subjects in the HER2-positive breast cancer cohort, 30-60 subjects in the first-line or  $\geq$  2nd-line HER2-positive gastric cancer cohort, and 20-26 subjects in other solid tumors. The sample size calculation is based on the estimate of the 95% CI for ORR using the Clopper Pearson method:

| Sampling Volume | Number of Subjects Achieving Objective Response | ORR, % | ORR 95% CI     |
|-----------------|-------------------------------------------------|--------|----------------|
| 20              | 8                                               | 40%    | (19.1%, 63.9%) |
|                 | 9                                               | 45%    | (23.1%, 68.5%) |
|                 | 10                                              | 50%    | (27.2%, 72.8%) |
|                 | 11                                              | 55%    | (31.5%, 76.9%) |
|                 | 12                                              | 60%    | (36.1%, 80.9%) |
|                 | 13                                              | 65%    | (40.8%, 84.6%) |
|                 | 14                                              | 70%    | (45.7%, 88.1%) |
|                 | 15                                              | 75%    | (50.9%, 91.3%) |
| 30              | 12                                              | 40%    | (22.7%, 59.4%) |
|                 | 14                                              | 47%    | (28.3%, 65.7%) |
|                 | 16                                              | 53%    | (34.3%, 71.7%) |
|                 | 18                                              | 60%    | (40.6%, 77.3%) |
|                 | 20                                              | 67%    | (47.2%, 82.7%) |
|                 | 22                                              | 73%    | (54.1%, 87.7%) |
|                 | 24                                              | 80%    | (61.4%, 92.3%) |
| 40              | 15                                              | 37.5%  | (22.7%, 54.2%) |
|                 | 20                                              | 50%    | (33.8%, 66.2%) |
|                 | 25                                              | 50%    | (45.8%, 77.3%) |
|                 | 30                                              | 60%    | (58.8%, 87.3%) |
|                 | 35                                              | 70%    | (73.2%, 95.8%) |
| 50              | 20                                              | 40%    | (26.4%, 54.8%) |

|    |    |       |                |
|----|----|-------|----------------|
|    | 25 | 50%   | (35.5%, 64.5%) |
|    | 30 | 60%   | (45.2%, 73.6%) |
|    | 35 | 70%   | (55.4%, 82.1%) |
|    | 40 | 80%   | (66.3%, 90.0%) |
| 60 | 25 | 41.7% | (29.1%, 55.2%) |
|    | 30 | 50%   | (36.8%, 63.2%) |
|    | 35 | 58.3% | (44.9%, 70.9%) |
|    | 40 | 66.7% | (53.3%, 78.3%) |
|    | 45 | 75%   | (62.1%, 85.3%) |
|    | 50 | 83.3% | (71.5%, 91.7%) |

## ANALYSIS SETS

The following analysis sets will be used for statistical analysis and data reporting.

### Safety Set

The safety set (SS) includes all subjects who have received at least 1 full or partial dose of KN026 and/or KN046. Subjects will be categorized according to the treatment groups planned in the protocol. All raw data will be counted using SS, which will be the default analysis set used for all analyses unless otherwise noted.

Subjects who fail screening will be only listed, but not summarized for analysis.

### Efficacy Analysis Set

The Efficacy Analysis Set (EAS) includes all subjects who have received at least 1 full or partial dose of KN026 and/or KN046 and have at least one postbaseline tumor imaging evaluation. This analysis set will be used for supportive analyses.

### PK Analysis Set

The PK analysis set includes subjects who have received at least 1 full or partial dose of KN026 and/or KN046 and have at least 1 post-dose PK sample for analysis.

### Immunogenicity Analysis Set

The immunogenicity analysis set includes subjects who have received at least 1 full dose or partial dose of KN026 and/or KN046 and have at least 1 post-dose immunogenicity sample for analysis.

## **DEMOGRAPHICS AND OTHER BASELINE CHARACTERISTICS**

Demographic and other baseline data, including age, sex, body height, weight, ECOG score, etc. will be presented for each subject in the study report and summarized by dose level using descriptive statistics (continuous data) or frequency tables (categorical data).

## **ANALYSIS OF THE PRIMARY ENDPOINT**

ORR and DOR: The 95% CIs calculated by Clopper Pearson method will be reported by cohort based on the SS; and the parameters of the time-related event (DOR) will be calculated using the Kaplan-Meier method by cohort.

## **ANALYSIS OF THE SECONDARY ENDPOINTS**

### **Safety Endpoints**

Actual cumulative dose and duration of exposure (days), dose intensity (calculated ratio of actual dose to actual treatment duration), relative dose intensity (calculated ratio of dose intensity to planned dose/planned treatment duration), number of dose delays, and treatment discontinuations will be listed and summarized for KN046 and KN026.

Safety analyses will be performed based on the Safety Analysis Set. Descriptive statistical analyses of safety endpoints will be performed by dose level. Safety analyses will be based on the incidence of treatment-emergent AEs (TEAEs), adverse events of special interests, immune-related AEs (irAEs), treatment-related AEs (TRAEs), Grade 3 or higher TEAEs, Grade 3 or higher irAEs and Grade 3 or higher TRAEs, and changes in vital signs, ECG, body weight, ECOG PS score, and laboratory values (hematology and serum chemistry). A treatment-emergent adverse event (TEAE) is defined as AEs from the first dose of KN026 and KN046 until 90 days after the last dose of KN046 (or 30 days after the last dose of KN026) or until 1 day before the initiation of a new anti-tumor therapy, whichever occurs first.

Treatment-emergent serious adverse events (TESAEs), immune-related adverse events (irAEs), and treatment-related adverse events (TRAEs) are defined as AEs from the first dose of KN026 and KN046 until 90 days after the last dose of KN046 (or 30 days after the last dose of KN026), or until 1 day before the initiation of a new anti-tumor therapy, whichever occurs first.

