| Urinalysis                                                               | X     | Every 12 weeks, or as clinically indicated                                                            |  |  |  |  |  | X   | (X)  |     |                            |  |
| Thyroid function                                                                     | X                 | Every 6 weeks, or as clinically indicated                                                             |  |  |  |  |  | X   | (X)  |     |                            |  |
| LVEF                                                                                 | X                 | Every 9 weeks, or as clinically indicated                                                             |  |  |  |  |  | X   |                  | X   | Every 3 months till 1 year |  |
| Troponin                                                                             | X                 | If clinically indicated                                                                               |  |  |  |  |  |     |                  |     |                            |  |
| IL-6                                                                                 |                   | If clinically indicated                                                                               |  |  |  |  |  |     |                  |     |                            |  |
| Serum pregnancy test (if applicable)                                                 | (X)  |                                                                                                       |  |  |  |  |  | (X) |                  |     |                            |  |
| Urine pregnancy test (if applicable)                                                 |                   | (Every 12 weeks)                                                                                      |  |  |  |  |  |     |                  |     |                            |  |
| Follicle-stimulating hormone (only if confirmation of menopausal status is required) | (X)               |                                                                                                       |  |  |  |  |  |     |                  |     |                            |  |

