4 After the subject signs the informed consent form, all adverse events need to be recorded until 30 days after the last dose of KN046 and/or KN026 or initiation of a new anti-tumor therapy, whichever occurs first. SAEs and TRAEs will be collected up to 90 days after the last dose of KN046 or 30 days after the last dose of KN026, whichever occurs later. The investigator is required to monitor adverse events until stable or until the outcome is known, unless the subject is recorded as "lost to follow-up". In the event of treatment-related serious adverse events (SAEs) of KN046 and/or KN026, they need to be recorded whenever they occur and regardless of the time from discontinuation of KN046 and/or KN026, and reported to regulatory authorities in accordance with local regulations; the symptomatic left ventricular systolic dysfunction and asymptomatic left ventricular systolic dysfunction ( $\geq 10\%$  and  $< 50\%$  decrease in LVEF from baseline) within 12 months after the last dose of KN026 should be recorded and reported as AEs, and those meeting the criteria for SAEs should be reported to regulatory authorities in accordance with local regulations;

5 The safety laboratory evaluations should be obtained prior to dosing; the pre-dose safety laboratory evaluations on Cycle 1 Day 1 should be performed at screening. The safety laboratory evaluations should include: blood count and differential, coagulation tests (PT/INR/aPTT/TT), serum chemistry, urinalysis, thyroid function (TSH/total T3/free T3/free T4), troponin, HBV/HCV/HIV, and serum/urine pregnancy test. The blood count and differential, coagulation tests (PT/INR/aPTT/TT), serum chemistry, and urinalysis at screening are required to be obtained within 7 days (inclusive) prior to the first dose and used for evaluation of inclusion/exclusion criteria. Refer to Section 7.2.3 for detailed description;

6 Blood count and differential include: red blood cell count (RBC), hematocrit, hemoglobin, mean hemoglobin content (MCH), mean hemoglobin concentration (MCHC), mean corpuscular volume (MCV), platelet count, white blood cell count WBC, neutrophil count and percentage, lymphocyte count and percentage, monocyte count and percentage, basophil count and percentage, eosinophil count and percentage;

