##### **Secondary Objectives**

- To evaluate the safety and tolerability of KN026 in combination with KN046;
- To evaluate the effect of HER2 amplification on the efficacy of KN026 in combination with KN046 (as supported by data);
- To evaluate the effect of HER2 expression levels (IHC1+ vs. IHC2+ vs. IHC3+) on the efficacy of KN026 in combination with KN046;
- To evaluate the effect of KN026 and KN046 drug exposure levels on anti-tumor activity;
- To evaluate immunogenicity of KN026;
- To evaluate immunogenicity of KN046.

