##### **Secondary Endpoints**

- Progression free survival (PFS), progression-free survival rate (PFSR) at 6 and 12 months, clinical benefit rate (CBR; defined as CR, PR, or SD  $\geq$  24 weeks) as judged by the investigator according to RECIST 1.1 criteria;
- Overall survival (OS), overall survival rate (OS rate) at 6 and 12 months;
- Frequency and severity of adverse events (AEs) (NCI CTCAE 5.0); changes in vital signs, physical examinations, electrocardiograms, and safety laboratory measures;
- Correlation between biomarkers (HER2 IHC, HER2 amplification) and clinical efficacy variables (ORR, CBR, PFSR, etc.);

Version No.: 4.2

- Correlation of KN026 and KN046 exposure levels ( $C_{\max,ss}$ ,  $AUC_{ss}$ ,  $C_{\text{trough},ss}$ ,  $C_{\text{avg},ss}$ , etc.) with efficacy variables (ORR, DOR, CBR, etc.) and safety variables (QTc and LVEF);
- Incidence and titer of anti-KN026 antibody (ADA); incidence of KN026 neutralizing anti-drug antibody (NADA) in subjects with high ADA titer;
- Incidence and titer of anti-KN046 antibody (ADA); incidence of KN046 neutralizing anti-drug antibody (ADA) in subjects with high ADA titer.

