### **Safety Evaluation**

Each subject will be monitored for safety in this study, including hematology, blood chemistry and electrolytes, coagulation, urinalysis, 12-lead ECG, ECHO/MUGA, physical examination, vital signs, height, weight, ECOG score, endocrine test, and immunogenicity test. Detailed tests and frequencies are presented in Table 1.

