***Other Safety Data (Physical Examination, ECG and Vital Signs)***

All ECG parameters, including the QT interval corrected according to the Fridericia method (QTc interval) for each subject, will be listed, and descriptive statistical analysis will be performed on the change from baseline for each parameter by dose level and evaluation time. Dose groups as well as correlations of changes in PK parameters (e.g.,  $C_{max}$ ,  $AUC_{0-t}$ ) and QTc will be presented graphically.

Blood pressure, pulse, respiratory rate, body temperature, and body weight will be listed for all subjects, and changes from baseline for each value will be presented and statistically described.

All physical examination findings will be listed.

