**Correlation between Pharmacokinetic and Clinical Efficacy Variables**

Logistic regression analysis will be conducted on AUC ( $AUC_{0-t}$ ,  $AUC_{inf}$ , and  $AUC_{last}$ ),  $C_{trough}$  and  $C_{max}$  versus clinical efficacy variables (ORR, CBR, PFS rate, and OS rate).

Data for AUC can be derived from the results of population pharmacokinetic analysis.

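### Section 8.2 and Table 1 footnote 4 put the 50% limit on the size of the LVEF fall, while Section 8.2.2 puts it on the LVEF reached and adds a category for falls of at least 15%

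*Protocol*

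**What the plan says.** Two places set the recording rule for the year after treatment: Section 8.2 (Documentation and Reporting of Adverse Events) and Table 1 footnote 4. Both describe asymptomatic left ventricular systolic dysfunction in a parenthesis as at least 10% and less than 50%, followed directly by the words "decrease in LVEF from baseline) within 12 months after the last dose of KN026 should be recorded and reported as AEs". Grammatically, both percentages describe the size of the decrease.

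Section 8.2.2 (Adverse Events of Special Interest) defines the asymptomatic event by two alternatives: a fall of at least 10% from baseline with an absolute LVEF below 50%, or a fall of at least 15% from baseline. It covers the time from KN026 dosing through 1 year after the last dose.

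LVEF is collected on a schedule. Section 7.2.3 lists "12-lead ECG, ECHO/MUGA, physical examination, vital signs" among the safety evaluations. Table 1 has LVEF every 9 weeks on treatment and then "Every 3 months till 1 year". Entry requires LVEF of at least 50% (I07). Table 6 (Section 6.2.3.3) and exclusion criterion E02 express LVEF falls as absolute decreases; Sections 8.2 and 8.2.2 do not say whether the fall is absolute or relative.

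Section 9.6.1 bases the safety analyses on the incidence of adverse events, including those of special interest, and on "changes in vital signs, ECG, body weight, ECOG PS score, and laboratory values (hematology and serum chemistry".

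**The concern.** Both sections describe the same clinical event over the same year, and they describe it differently. A site following Section 8.2 or the flow-chart footnote and a site following Section 8.2.2 would file different asymptomatic falls. For most of that year the general adverse event window has closed (30 days after the last dose, or the start of a new anti-tumor therapy), so these clauses largely decide whether an asymptomatic fall becomes an event record.

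What is at stake is the consistency of the cardiac adverse event counts. Section 9.6.1 names "changes in vital signs, ECG, body weight, ECOG PS score, and laboratory values (hematology and serum chemistry" as the measured changes it will analyse; LVEF is not among them. In the protocol's own text, LVEF falls reach the results mainly as adverse events and events of special interest, and a count built on two definitions is hard to interpret. This is a recording rule for sites, so a statistical analysis plan cannot repair it.

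**Working it through.** The protocol gives no figure that rests on this definition, so there is none to reproduce. The check applies each rule to the same baseline and follow-up values.

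**Inputs.** Section 8.2 and footnote 4: fall of at least 10% and less than 50%. Section 8.2.2: fall of at least 10% with absolute LVEF below 50%, or fall of at least 15%. I07: baseline of at least 50%. Table 6 and E02: falls in absolute terms. Assumption for the counts only: whole-point baselines from 50 to 75 and follow-up values down to 15.

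**Rules in absolute points.** Let b be baseline, v the follow-up value and a = b − v.

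- Section 8.2, literal: 10 ≤ a < 50
- Section 8.2, probable intent: a ≥ 10 and v < 50
- Section 8.2.2: (a ≥ 10 and v < 50) or a ≥ 15

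**Step 1, literal wording against Section 8.2.2.** If b is below 60, any fall of 10 or more gives v < 50, so the rules agree. They differ when 10 ≤ a < 15 and v ≥ 50, which needs b ≥ 60. For b from 60 to 64 the extra falls run from 10 to b − 50; from b = 65 upward they fill the whole band from 10 to under 15. On the grid, baselines 60 to 64 give 1 + 2 + 3 + 4 + 5 = 15 pairs and baselines 65 to 75 give 11 × 5 = 55, so 70 pairs are reportable only under Section 8.2. In the other direction only falls of 50 points or more differ, which on this grid means follow-up values of 25 or lower; that has no practical weight.

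**Step 2, probable intent against Section 8.2.2.** The intended rule adds nothing beyond Section 8.2.2 but misses a ≥ 15 with v ≥ 50, which needs b ≥ 65. On the grid: 1 + 2 + … + 11 = 66 pairs.

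**Step 3, relative falls.** With the fall as 100 × a / b, 60 to 30 gives 100 × 30 / 60 = 50.0%. That is not below 50%, so literal Section 8.2 excludes it while Section 8.2.2 includes it. For 70 to 60, 100 × 10 / 70 = 14.3%, which Section 8.2 includes and Section 8.2.2 does not.

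| Baseline to follow-up | Fall (points) | 8.2 literal | 8.2 probable intent | 8.2.2 |
|---|---|---|---|---|
| 70 to 60 | 10 | yes | no | no |
| 60 to 48 | 12 | yes | yes | yes |
| 70 to 55 | 15 | yes | no | yes |
| 60 to 30 | 30 | yes (no if relative) | yes | yes |

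None of the three readings makes the two sections agree.

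**Step 4, after the fix.** If Section 8.2 and footnote 4 carry both Section 8.2.2 categories, in points, the rules are identical for every pair.

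**The case against.** The strongest reply is that nothing is lost. Section 8.2.2 requires every event of special interest to go on the adverse event form of the eCRF, serious or not, through 1 year after the last KN026 dose. Anything meeting its two categories is therefore captured whatever Section 8.2 says, including 70 to 55 and 60 to 30. This stands, and it limits the point.

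Second, the Section 8.2.2 list is inclusive: it asks for all cardiac adverse events and introduces the categories as examples of what is included. A fall from 70 to 60 filed under Section 8.2 is not forbidden by Section 8.2.2. This also stands, so the literal wording produces extra, conservative reporting rather than prohibited reporting.

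Third, the two sections set different duties, adverse event recording and 24-hour reporting, and a wider net for the first would not in itself be a contradiction. That would persuade if the wider net looked deliberate. It does not: an upper limit of 50 points on a fall does almost no work, and the same 50% appears in Section 8.2.2 as the LVEF reached.

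Fourth, 70 and 66 are unweighted counts on a grid, not event frequencies. Agreed; they show where the rules part, not how often.

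**Conclusion.** The definition in Section 8.2 and footnote 4 is wrong as written and conflicts with Section 8.2.2 under the literal, relative and probable-intent readings. The size is minor. The main practical effect of the literal reading is that falls of 10 to under 15 points with LVEF still at 50% or above, in subjects with baseline of at least 60%, become mandatory adverse events under one section and fit neither category of the other. The size rests on reading falls as absolute points, as Table 6 does. How many subjects would be affected cannot be derived from the protocol.

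Three stronger readings are not supported. A reader might infer that cardiac events would be missed; the special-interest rule captures them. A reader might infer that subjects are less well protected; the LVEF schedule and the dose rules in Table 6 do not use this definition.

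A reader might also infer that a secondary endpoint has no analysis. Section 3.2.2 lists correlation of exposure with "safety variables (QTc and LVEF". Section 9 mentions "Dose groups as well as correlations of changes in PK parameters" with QTc, otherwise relates exposure "versus clinical efficacy variables (ORR, CBR, PFS rate, and OS rate", and never names LVEF. But Section 3.2.2 still commits to that correlation, Section 9.1 leaves specific methods to the SAP, which is not shown, and nothing in Section 9 excludes an LVEF analysis. Section 9 is a summary; its exposure-efficacy list also omits DOR, which Section 3.2.2 names. The matching objective, "To evaluate the effect of KN026 and KN046 drug exposure levels on anti-tumor activity", does not mention safety, and the list of measured changes in Section 9.6.1 broadly follows the safety endpoint in Section 3.2.2, which does not name LVEF either. That question belongs to the SAP.

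**What to change.** In Section 8.2 and Table 1 footnote 4, replace the parenthesis with: fall of at least 10 percentage points from baseline with absolute LVEF below 50%, or fall of at least 15 percentage points from baseline. In Section 8.2.2, state that both falls are in absolute percentage points, as in Table 6. Table 6 stays as it is.

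The cost is a few words in three places, with no change to assessments, sample size or dose rules. One thing is given up: falls of 10 to under 15 points with LVEF still at 50% or above are no longer adverse events by threshold alone. Those judged clinically significant would still be recorded under Section 8.2.3, and the LVEF values are still collected on the Table 1 schedule.

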| Tumor imaging (thoracic/abdominal/pelvic)                            | X                 | Every 6 weeks (± 7 days); from 48 weeks onwards: every 12 weeks (± 7 days)                            |  |  |  |  |  | (X) | (X)              | (X) | (X)                        |  |
| Tumor imaging (brain, if applicable)                                 | (X)               | (if clinically indicated)                                                                             |  |  |  |  |  |     |                  |     |                            |  |
| Bone scan (if applicable)                                               | (X)               | (if clinically indicated)                                                                             |  |  |  |  |  |     |                  |     |                            |  |

| Study Drug Administration                |  |   |   |  |   |  |  |                            |  |  |  |  |
|------------------------------------------|--|---|---|--|---|--|--|----------------------------|--|--|--|--|
| KN046 administration (Q3W)  |  | X |   |  | X |  |  | Administration on Day 1/21 |  |  |  |  |
| KN026 administration (Q3W)  |  | X | X |  | X |  |  | Administration on Day 1/21 |  |  |  |  |

1 The EOT visit may be performed on the day of the decision to discontinue KN026 and KN046 treatment, and the same EOT test may not be repeated if it is performed within 7 days after the last pre-treatment evaluation;

2 The 30- and 90-day safety follow-up visits will be performed after the end of all study treatments. For subjects who discontinue KN046 treatment first and continue to receive KN026, the 90-day safety follow-up visit is not required if 30 days after the last dose of KN026 are later than 90 days after the last dose of KN046;

3 All concomitant medications/procedures from 28 days prior to dosing to 30 days after the last dose of KN046 and/or KN026 should be recorded. Concomitant medications/procedures after the 30-day safety follow-up period are also to be recorded as part of SAE recording, analysis, and reporting if they are performed for the purpose of treating SAEs related to KN046 and/or KN026;

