### **30-Day and 90-Day Safety Visits**

A safety follow-up visit is required for subjects 30 days ( $\pm 3$  days) after the last dose of KN026 and/or KN046 and 90 days ( $\pm 7$  days) after the last dose of KN046. For subjects who discontinue KN046 treatment first and continue to receive KN026, the 90-day safety follow-up visit is not required if 30 days after the last dose of KN026 are later than 90 days after the last dose of KN046.

After the EOT visit, AEs need to be recorded up to 30 days after the last dose of study drug. Thereafter, all SAEs and treatment-related non-serious AEs (including irAEs) will be recorded until 90 days after the last dose of KN046. SAEs that persist after the 30-day or 90-day safety follow-up visit are required to be monitored by the investigator until stabilization or until the outcome is known.

Subsequent anti-tumor therapies, tumor imaging evaluations (see Section 7.2.2, if applicable), etc. will also be collected during the safety follow-up period. Please refer to Table 1 for the contents of visits during the safety follow-up period.

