## **DOCUMENTATION AND REPORTING OF ADVERSE EVENTS**

This study requires documentation of any untoward medical occurrence during the study after signing the ICF until 30 days after the last dose of study treatment or initiation of a new anti-tumor therapy, whichever occurs first. SAEs and TRAEs will be collected up to 90 days after the last dose of KN046 or 30 days after the last dose of KN026, whichever occurs later. SAEs suspected to be related to study drug should be recorded and reported at any time, regardless of the time from discontinuation of study drug. The symptomatic left ventricular systolic dysfunction and asymptomatic left ventricular systolic dysfunction ( $\geq 10\%$  and  $< 50\%$  decrease in LVEF from baseline) within 12 months after the last dose of KN026 should be recorded and reported as AEs, and those meeting the criteria for SAEs should be reported to regulatory authorities in accordance with local regulations.

The investigator will grade each AE according to NCI-CTCAE 5.0. If the severity/intensity of a particular AE is not specifically graded by the guideline, the investigator will grade in accordance with the following general definitions of Grade 1 through Grade 5, with his/her best medical judgment:

- Grade 1: Mild; asymptomatic or mild symptoms; clinical or diagnostic observations only; intervention not indicated;
- Grade 2: Moderate; minimal, local or noninvasive intervention indicated; limiting age-appropriate instrumental activities of daily living (ADL) (e.g., preparing meals, shopping for groceries, using the telephone, managing money, etc.);
- Grade 3: Severe; serious or clinically significant but not immediately life threatening; hospitalization or prolongation of hospitalization indicated; disabling; limiting self-care ADL (e.g., bathing, dressing and undressing, feeding self, using the toilet, taking medications), without bedridden;
- Grade 4: Life-threatening; urgent intervention indicated;
- Grade 5: Deaths related to AEs.

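### Section 9.6.1 ends the treatment-emergent window on a 'first' rule while SAEs and TRAEs are collected to the later drug limit, and on any other reading it has no rule for choosing between the two drugs

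*Protocol*

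**What the plan says.** **Analysis window.** Section 9.6.1 (Safety Endpoints) starts the TEAE window at the first dose. It ends the window 90 days after the last KN046 dose, followed in brackets by "or 30 days after the last dose of KN026) or until 1 day before the initiation of a new anti-tumor therapy, whichever occurs first". The next paragraph repeats the same limits and the same 'first' rule for TESAEs, irAEs and TRAEs.

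**Collection window.**
- Section 8.2 collects SAEs and TRAEs up to "90 days after the last dose of KN046 or 30 days after the last dose of KN026, whichever occurs later". Footnote 4 of Table 1 says the same. Neither cuts this collection at new therapy.
- Section 7.1.4 adds that, after the 30-day period, "all SAEs and treatment-related non-serious AEs (including irAEs) will be recorded until 90 days after the last dose of KN046".
- All other AEs are documented only "until 30 days after the last dose of study treatment or initiation of a new anti-tumor therapy, whichever occurs first" (Section 8.2).
- SAEs suspected to be drug-related "should be recorded and reported at any time, regardless of the time from discontinuation of study drug".

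**One drug may outlast the other.** Footnote 2 of Table 1 has a rule that begins "For subjects who discontinue KN046 treatment first and continue to receive KN026". Sections 6.1.4.1 and 6.1.4.2 each leave the investigator to decide, when one drug is stopped for an AE, whether the other goes on.

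**Tables planned.** Section 9.6.1 bases the safety analysis on the incidence of TEAEs, AESIs, irAEs and TRAEs and on Grade 3 or higher subsets. Its Adverse Event subsection also lists summaries of all AEs, SAEs, AEs leading to discontinuation, AEs leading to death, and AESIs, with no treatment-emergent window stated for these.

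**The concern.** The analysis and collection rules use the same two post-dose limits but join them with opposite words. If the analysis window takes the earliest date, events that sites are told to record cannot be counted as treatment-emergent, treatment-related or immune-related. With two drugs that can stop at different times, the window can even close during dosing.

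Safety and tolerability is the first secondary objective (Section 3.1.2), and the affected categories are those that Section 9.6.1 names as the basis of the safety analysis. Section 7.1.4 asks sites to record irAEs to 90 days after KN046; a window that ends earlier would leave part of that follow-up out of the irAE incidence.

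**Working it through.** The plan gives no figure to reproduce. The check is day arithmetic on the stated limits. The dosing and new-therapy days below are illustrative assumptions.

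**Definitions**
- A = last KN046 day + 90
- B = last KN026 day + 30
- C = new-therapy day − 1
- End of SAE/TRAE collection = max(A, B)

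**Readings of the end of the window in Section 9.6.1**
- (i) literal, earliest of all three: min(A, B, C)
- (ii) KN046 limit, 'first' applying to new therapy only: min(A, C)
- (iii) KN026 limit, likewise: min(B, C)
- (iv) later drug limit, then new therapy: min(max(A, B), C)

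| Scenario | A | B | C | Collection ends | (i) | (ii) | (iii) | (iv) |
|---|---|---|---|---|---|---|---|---|
| Both stop day 0 | 90 | 30 | none | 90 | 30 | 90 | 30 | 90 |
| KN046 stops day 0, KN026 to day 63 | 90 | 93 | none | 93 | 90 | 90 | 93 | 93 |
| KN046 stops day 0, KN026 to day 180 | 90 | 210 | none | 210 | 90 | 90 | 210 | 210 |
| KN026 stops day 0, KN046 to day 180 | 270 | 30 | none | 270 | 30 | 270 | 30 | 270 |
| Both stop day 0, new therapy day 21 | 90 | 30 | 20 | 90 | 20 | 20 | 20 | 20 |
| Both stop day 0, new therapy day 45 | 90 | 30 | 44 | 90 | 30 | 44 | 30 | 44 |

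**Days collected but not counted, no new therapy**
- Reading (i), both stop together: 90 − 30 = 60 days.
- Reading (i), KN026 continues to day 63: 93 − 90 = 3 days, none of them on drug.
- Reading (i), KN026 continues to day 180: 210 − 90 = 120 days, of which 180 − 90 = 90 are on KN026.
- Reading (i), KN046 continues to day 180: 270 − 30 = 240 days, of which 180 − 30 = 150 are on KN046.
- Reading (ii): no loss when both stop together or when KN046 continues. When KN026 continues to day 180, the same 120 days are lost, 90 of them on KN026.
- Reading (iii): no loss when KN026 continues. Days 31–90 are lost when both stop together (60 days). When KN046 continues to day 180, 240 days are lost, 150 of them on KN046.
- Reading (iv): no loss.

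**With new therapy.** Even under (iv) a gap stays: 90 − 20 = 70 days for new therapy on day 21, and 90 − 44 = 46 days for day 45. The analysis cuts at new therapy and SAE/TRAE collection does not.

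**All-cause counts.** Non-serious unrelated AEs are collected to 30 days after the last dose, or new therapy if earlier. If both drugs stop on day 0, a window to day 90 includes 90 − 30 = 60 days in which such events are not sought. An all-cause incidence over that window would mix complete and incomplete ascertainment.

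**The case against.** The best defence is grammatical. The KN026 limit sits in brackets inside the first of two 'until' clauses, so 'first' may choose only between the post-dose limit and new therapy. If the later-of-two rule of Section 8.2 is then carried over, the gap closes unless new therapy starts. This is a fair reading, so the 60-day and on-drug losses cannot be called certain. It does not rescue the sentence, though. Section 9.6.1 does not contain the later-of-two rule, and without it the choice between drugs is open; each drug's limit taken alone still loses time in some scenario above.

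A reader might infer that the late events vanish from the safety report. The documents do not support that. The all-AE, SAE, death and AESI summaries carry no stated window, and the AESI list in Section 8.2.2 includes immune-related pneumonia, colitis and nephritis of Grade 3 or higher, specified severe hepatitis, and myocarditis of any grade. What is affected is the TEAE, TESAE, TRAE and irAE categories.

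A reader might also infer that the bias is worst in subjects who stop KN046 and stay on KN026. Nothing shows this: on the literal reading the reverse case loses more days (240 against 120).

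It can also be said that the study is descriptive, that the primary endpoints are untouched, and that an SAP could settle the rule. The first two stand and limit the severity. The third carries less weight, because the protocol does not leave the window to the SAP: it states one, twice.

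**Conclusion.** The point holds as a contradiction between the analysis and collection windows, together with a missing selection rule. On the literal reading, 60 days of collected SAE, TRAE and irAE follow-up fall outside the four treatment-emergent categories when both drugs stop together, and the window can close during continued single-drug treatment. On the narrower reading the loss depends on which drug limit the programmer picks. On every reading, SAEs and TRAEs collected after new therapy fall outside the definitions.

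The figures are days of follow-up, not events. The documents do not say how many subjects will continue on one drug or how many events will fall in the gap, so no bias in incidence can be quantified. Its direction, where there is one, is towards lower TRAE, irAE and TESAE incidences. Collection itself is adequate and no data are lost. Severity: should-fix.

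**What to change.** In Section 9.6.1, and in the SAP to match:

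1. End the treatment-emergent window at the later of 90 days after the last KN046 dose and 30 days after the last KN026 dose, or 1 day before new anti-tumor therapy if that is earlier.
2. Use this single window for TEAEs, TESAEs, TRAEs and irAEs. Separate windows, such as 30 days for TEAEs and 90 for TESAEs, would make an SAE on day 60 a TESAE without being a TEAE.
3. Restrict the all-cause incidence table that includes non-serious unrelated AEs to 30 days after the last dose of whichever drug stops last, or new therapy if earlier, since such events are not collected afterwards.
4. State that SAEs and TRAEs collected after new therapy starts are summarised separately. The new-therapy cut-off then stays in the main tables, so events arising under a later treatment are not attributed to this one, and the collected data are still reported.

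The cost is a wording change, a little more table work, and probably slightly less favourable TRAE, irAE and TESAE incidences. Collection does not change.
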